## Abstract

**Introduction::**

Over the last 10 years, it has been demonstrated that photobiomodulation therapy (PBMT), also known as phototherapy, using low-level laser therapy (LLLT) and/or light-emitting diode therapy (LEDT) has ergogenic effects, improving athletic performance and also accelerating post-exercise recovery. However, many aspects related to these effects and its clinical applicability remain unknown. Therefore, the aim of this project is to evaluate the ergogenic effects of PBMT in detraining after an aerobic endurance training protocol.

**Methods and analyzes::**

A randomized, triple-blind, placebo-controlled clinical trial will be carried out. Healthy male volunteers will be randomly distributed into 4 experimental groups: PBMT before and after training sessions + PBMT during detraining, PBMT before and after training sessions + placebo during detraining, placebo before and after training sessions + PBMT during detraining, and placebo before and after training sessions + placebo during detraining. The aerobic endurance training sessions will be carried out using motorized treadmills during 12 weeks, and the detraining period will consist in the next 4 weeks after that. It will be analyzed the time until exhaustion, maximal oxygen uptake (VO_2max_), and fat percentage of volunteers.

**Discussion::**

Despite the increasing body of evidence for the use of PBMT as an ergogenic agent, several aspects remain unknown. The findings of this study will contribute to the advance of knowledge in this field regarding clinical applications.

**Ethics and dissemination::**

This study was approved by the Research Ethics Committee of Nove de Julho University. The results from this study will be further disseminated through scientific publications in international peer-reviewed journals and presentations at national and international scientific meetings.

**Trial registration number::**

NCT03879226.

## Introduction

1

Photobiomodulation therapy (PBMT), also known as phototherapy, is a nonthermal process where light interacts with chromophores leading to photo-induced reactions in different tissues. PBMT uses nonionizing light sources, such as lasers, light-emitting diodes (LEDs), and broadband light, from the visible to the infrared spectrum.^[1]^

In 2008, the first randomized controlled trial (RCT) investigating the use of PBMT for athletic performance enhancement was published.^[2]^ This pioneer RCT showed for the very first time that the use of PBMT before an exercise session could enhance athletic performance of high-level athletes, as well as decrease the delayed onset muscle fatigue and prevent the expected increase of blood lactate levels.

Subsequently, a series of clinical studies involving athletes from different sports and healthy individuals conducted by our research group and others showed that, when applied before an exercise session, PBMT can increase the number of repetitions performed,^[2–4]^ lengthen the time to exhaustion,^[2,5–7]^ increase peak torque,^[4,8–11]^ and even improve performance of athletes in field tests,^[12]^ in simulated^[13]^ and real matches.^[14]^ Moreover, studies have also shown that PBMT can potentiate gains in different training protocols, such as strength training^[15,16]^ and aerobic training.^[17]^

Despite the remarkable, and fast progress of the knowledge in this field, which culminated in the publication of 3 systematic reviews^[18–20]^ with meta-analyses^[19,20]^ evidencing the ergogenic effects of PBMT, there are some key aspects that remain unknown and must be investigated. Among them, we highlight the potentially beneficial effects of PBMT during the detraining period after aerobic endurance training protocols.

Various clinical training methods and protocols for performance enhancement, health promotion, and rehabilitation are used by different groups, including athletes, physically active individuals, sedentary individuals, and patients with different disorders and diseases. Among the training types and protocols, aerobic endurance training stands out. However, training protocols very often require discontinuation due to illness, injury, or other factors that may alter the capacity for physical activity, thereby causing a rapid loss of aerobic endurance conditioning,^[21]^ which represents a challenging problem in clinical practice. It should also be noted that, thus far, no evidence or consensus on any particular resource or method that may decrease the effects of detraining has been found.

An interesting study conducted by Wasik et al^[22]^ assessed the effects of PBMT on the oxidative metabolism of peripheral blood cells (erythrocytes, granulocytes, and lymphocytes) by irradiating heparinized blood samples from 15 volunteers. After irradiation, partial pressure of oxygen (PO_2_) and oxygen saturation (SaO_2_) increased, which shows that PBMT-induced photochemical reactions in blood cells may enhance the oxygen-carrying ability of blood. These interesting findings suggest that PBMT may attenuate the loss of performance observed during the detraining period after an aerobic endurance training program because oxygen transport and, consequently, the ability of muscles to use it, decrease during the detraining period.

Therefore, the effects of PBMT on aerobic endurance detraining remain unknown and it is a scientific challenge that will represent a key advance in the knowledge of this field when it is overcome. With this aspect in mind, this project aims to assess the ergogenic effects of PBMT during the detraining period after completing an aerobic endurance training protocol.

## Methods and analyses

2

### Design and ethical aspects

2.1

A randomized, triple-blind (volunteers, therapists, and assessors), placebo-controlled clinical trial will be performed at Laboratory of Phototherapy and Innovative Technologies in Health. The study will follow the ethical guidelines and was approved by the Research Ethics Committee of Nove de Julho University (protocol number 1781602). Moreover, this protocol was prospectively registered at ClinicalTrials.org (NCT03879226). All volunteers will sign an informed consent at the time of enrolment in this study.

### Subjects and sample size

2.2

As no studies assessing the effects of PBMT during the detraining period after an aerobic training program are currently available, the number of participants per group in the present study was calculated based on a pilot study, with 5 volunteers per group, which was conducted by our research group in order to estimate the sample size. A β value of 20% and an α of 5% were used to calculate the sample size.

The pilot study showed that applying PBMT during the detraining period resulted in a time to exhaustion (primary outcome of this study) of 923.60 seconds (65.77 standard deviation) during the progressive treadmill test, whereas applying the placebo during the detraining period resulted in a time to exhaustion of 846.82 seconds (99.23 standard deviation). We used the Researcher's Toolkit to calculate the sample (https://www.dssresearch.com/KnowledgeCenter/toolkitcalculators/samplesizecalculators.aspx).

On the basis of the aforementioned parameters used to calculate the sample, we found 15 volunteers per group, for a total of 60 volunteers. Therefore, predicting a 20% sample loss, 72 healthy, physically inactive male volunteers aged from 18 to 35 years will be recruited for the study to ensure a final sample size of 60 volunteers. As the PBMT device used in the study causes no harmful thermal effects,^[23]^ volunteers of different skin colors will be recruited.

Volunteers will be informed about all study procedures and will be asked to sign the Informed Consent Form before their enrollment in the study.

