## Discussion

3

The effects of PBMT on the maintenance of gains from an aerobic endurance training protocol during a period of discontinuation of physical activity, that is, a detraining period, have not yet been investigated. We believe that PBMT will have a positive effect on the maintenance of gains from aerobic endurance training, during the detraining period. Given that that many individuals, whether they are athletes or not, often fail to maintain training routines, the ability to minimize this loss would be of significant value in terms of accelerating the return to their previous fitness levels.

As strengths of this study, we can highlight that it has high methodological quality, as it is a randomized, controlled, and prospectively registered clinical trial. Another strength is that it has a triple blinded design, which means that outcome assessors, therapists, and patients will be blinded to interventions over the course of the study.

In addition, the sample size was calculated based on a pilot study to provide the appropriate statistical power to detect precise differences for the primary outcome of the study. And finally, the doses, sites of application, and the moment to apply PBMT were previously optimized and published in international peer-reviewed journals.

Despite this study will analyze the effects of PBMT only until 4 weeks of detraining after 12 weeks of strength training, it is important to stress that such aspect never was investigated previously. And therefore, we believe that the present project is a major step toward the widespread use of PBMT as an ergogenic agent for not only increasing performance but also decreasing losses incurred by detraining. These factors have a direct impact on clinical practice, not only to athletes but also to patients in physical rehabilitation programs, when performing aerobic endurance training is not possible.

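### A pilot of 5 men per group, reported only as post-detraining times (difference 76.78 s, 95% CI about -46 to +200 s), is too imprecise to support the Discussion's claim of appropriate power

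*Protocol article*

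**What the plan says.** Section 2.2 (Subjects and sample size) explains that no earlier study of PBMT in detraining after aerobic training was available, so "the number of participants per group in the present study was calculated based on a pilot study, with 5 volunteers per group", the pilot having been run by the same research group. It reports one mean and SD per condition. PBMT during detraining gave a time to exhaustion "of 923.60 seconds (65.77 standard deviation) during the progressive treadmill test"; for the comparator, "applying the placebo during the detraining period resulted in a time to exhaustion of 846.82 seconds (99.23 standard deviation"). The error rates are given without sidedness: "A β value of 20% and an α of 5% were used to calculate the sample size". The result is 15 per group, 60 in total across four groups.

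The section gives no week 12 value, no change over detraining, no SD of change and no confidence interval. The Introduction and Discussion describe the aim as limiting the loss during the detraining period, and section 2.4 schedules assessments at baseline and at weeks 4, 8, 12 and 16.

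The Discussion lists the calculation among the strengths of the study: "the sample size was calculated based on a pilot study to provide the appropriate statistical power to detect precise differences".

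**The concern.** A sample size holds its stated power only if the planning effect and SD are close to the truth. Here both are point estimates from very small groups, used without any allowance for their own error. They are also final treadmill times. If the two pilot sets differed in fitness at week 12, that difference is counted as an effect of PBMT during detraining.

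What is at stake is how the result will be read. A trial that advertises adequate power invites the reading that a non-significant result is evidence against a useful effect. If the true effect is smaller than the pilot's, or the SD larger, that reading is unsafe, and nothing in section 2.2 warns the reader.

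**Working it through.** **Inputs, all from section 2.2:** means 923.60 and 846.82 s; SDs 65.77 and 99.23 s; pilot of 5 per group; alpha 5%; beta 20%; 15 per group.

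**1. Reproduce the plan's figure.** Difference = 923.60 - 846.82 = 76.78 s. Sum of variances = 65.77² + 99.23² = 14,172.3. Pooled SD = √(14,172.3/2) = 84.18 s.

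n per group = 14,172.3 × (z_alpha + z_beta)² / 76.78²

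- One-sided: 14,172.3 × (1.645 + 0.842)² / 5,895.2 = 14.86, so 15. This matches the plan.
- Two-sided: 14,172.3 × (1.960 + 0.842)² / 5,895.2 = 18.87, so 19 (20 with the noncentral t).

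**2. Precision of the pilot difference.** Take each mean as 5 men.

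- SE = √(14,172.3/5) = 53.24 s; t = 76.78/53.24 = 1.44 on 8 df; two-sided p = 0.19.
- 95% CI = 76.78 ± 2.306 × 53.24 = -46.0 to +199.6 s (Welch: -49 to +203 s).
- 95% CI for the SD = 84.18 × √(8/17.53) to 84.18 × √(8/2.18) = 57 to 161 s.

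The number of pilot groups is not stated. If each mean combined two groups of 5, then SE = √(14,172.3/10) = 37.65 s and the CI is 76.78 ± 2.101 × 37.65 = -2.3 to +155.9 s. Zero is still included.

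**3. Power of 15 against 15 on unadjusted final times** (noncentral t, 28 df, no multiplicity correction):

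| Assumption | Two-sided 5% | One-sided 5% |
|---|---|---|
| Pilot values exactly true (76.78 s, SD 84.18 s) | 67% | 79% |
| Averaged over pilot uncertainty | 57% | 63% to 64% |
| Half the pilot effect (38.4 s), SD 84.18 s | 23% | 34% |

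For the averaged row, the variance is drawn as 8 × 84.18² / chi-square(8), and the true difference as normal around 76.78 s with SE = SD × √(2/5). This amounts to a flat prior for the effect and takes 5 men per pilot mean. It counts only significant results that favour PBMT. The like-for-like loss from pilot uncertainty is therefore 67% to 57% two-sided, or 79% to about 63% one-sided. The gap between columns is sidedness, a separate matter.

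The difference detectable with 80% power at two-sided 5% is about 89 s, which is larger than the planning effect.

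**4. What the change scale could do.** Assume equal SDs of 84.18 s at weeks 12 and 16 and correlation r between them. The SD of change is then 84.18 × √(2(1 - r)).

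| r (assumed) | SD of change | Detectable, 80% power, two-sided | Two-sided power at 38.4 s |
|---|---|---|---|
| 0.5 | 84 s | 89 s | 23% |
| 0.8 | 53 s | 56 s | 48% |
| 0.9 | 38 s | 40 s | 77% |

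The document gives no r and no SD of change, so no row can be chosen from it.

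**The case against.** The strongest defence is that the plan states its inputs openly, that no earlier study existed, and that 15 follows from those inputs. A pilot of this size is not meant to reach significance, so a CI that includes zero is not itself a fault. All of this stands. A reader might go on to infer that the sample size has no support at all; the documents do not bear that out, because the stated figure reproduces one-sided. The fault is to treat an imprecise estimate as known and then to present the result as adequate power.

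A second defence is that section 2.6 plans a repeated-measures analysis over time and group, and includes absolute values, so planning on levels matches one of the stated analyses. The low power figures in step 3 belong to an unadjusted week 16 comparison. This also stands. A reader might infer that a null result would be close to uninformative, but the table in step 4 shows that this depends on an unknown correlation: at r of 0.8 to 0.9, power at half the effect would be about 48% to 77%.

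A third tempting reading is that a 77 s difference would require PBMT to prevent the whole of the detraining loss. It would not. A placebo loss of 150 s that is half prevented gives 75 s. Section 2.2 also does not say what the pilot men received during training, so part of the difference could have arisen before detraining began. Nor can one say that losses of this size are unknown: the Introduction cites a source for rapid loss of conditioning, and pilot week 12 data may exist in the full protocol.

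None of this rescues the sentence in the Discussion, which is an affirmative claim in the article and not a detail left to another document.

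**Conclusion.** The point holds as a matter of imprecision and over-claiming. The planning difference of 76.78 s carries a 95% CI of about -46 to +200 s, or about -2 to +156 s on the more generous reading of the pilot. It is a difference in levels after detraining, with nothing given on the loss from week 12 to week 16 that the trial aims to limit. On unadjusted final times, 15 per group has about 67% power two-sided (79% one-sided) if the pilot is exactly right, and about 57% (63% to 64%) once its uncertainty is averaged in. These figures assume the pooled SD of 84.18 s, a flat prior and 5 men per mean for the averaged values, and no Bonferroni correction. They do not show that the trial is badly underpowered for an analysis of change, because the correlation that decides this is not reported. They do show that the pilot cannot support the power statement as written.

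**What to change.** Keep the sample size and change the text.

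- **Section 2.2:** report the pilot difference with its CI and the number of men behind each mean. State whether the test is one-sided or two-sided. Restate what 15 per group can detect: about 89 s on unadjusted final times at two-sided 5% and 80% power, before multiplicity correction. Add the power at half the pilot effect, about 23% two-sided.
- **Section 2.2, if the pilot men were tested at week 12:** add the between-group difference in week 12 to 16 change, its SD, and the detectable difference on that scale. Note that it may be smaller than 89 s if the visits are highly correlated (about 56 s at r = 0.8 with equal SDs), and that an estimate from the same few men remains imprecise.
- **Discussion:** replace the adequate-power claim with a statement that a non-significant result will be interpreted from its confidence interval.

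The cost is a short recalculation from data in hand and a few sentences. No extra volunteers are needed. The drawback is that the stated power becomes less favourable.

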### Statistical analysis

2.6

The primary outcome will be time until exhaustion obtained from progressive treadmill test. The secondary outcomes are VO_2max_ and fat percentage test. The intention-to-treat analysis will be followed a priori. All the data will be analyzed by a blinder researcher not involved in data collection. The findings will be tested for their normality using the Shapiro–Wilk test. Parametric data will be expressed as mean and standard deviation and nonparametric data as median and respective upper and lower limits. Parametric data will be analyzed by 2-way repeated measures analysis of variance (ANOVA; time vs experimental group) with post-hoc Bonferroni correction. Nonparametric data will be analyzed using the Friedman test and, secondarily, the Wilcoxon signed-rank test. Data will be analyzed in terms of both their absolute values and their percentage of change based on the values established in the baseline. The significance level will be set at *P* < .05.

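### The 15 per group follows from a one-sided, uncorrected comparison of two means; the two-sided equivalent needs 19 to 20, and 15 gives about 67–70% power, not 80%

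*Protocol article*

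**What the plan says.** All from the protocol article.

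- **Section 2.2, Subjects and sample size.** The size rests on "a pilot study, with 5 volunteers per group". Mean time to exhaustion was 923.60 s (SD 65.77) with PBMT during detraining and 846.82 s (SD 99.23) with placebo. On error rates: "A β value of 20% and an α of 5% were used to calculate the sample size". The result from an online calculator: "we found 15 volunteers per group, for a total of 60 volunteers". To allow for loss, 72 are recruited. The section mentions neither sidedness nor multiplicity.
- **Section 2.6, Statistical analysis.** Time to exhaustion is primary. Parametric data go to a two-way repeated-measures ANOVA (time by experimental group) "with post-hoc Bonferroni correction", both as absolute values and as percentage change from baseline. "The significance level will be set at" P < .05. No one-sided test is declared, and the number of comparisons under Bonferroni is not given.
- **Section 3, Discussion.** The pilot-based calculation is listed as a strength that serves "to provide the appropriate statistical power to detect precise differences for the primary outcome of the study".

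**The concern.** Section 2.2 prints every input and the result, so the calculation can be repeated. A conventional two-sided calculation does not return 15. A one-sided one does, but nothing in section 2.6 is one-sided: the ANOVA F test has no direction, and Bonferroni makes each pairwise threshold stricter than 5%. The comparison that was sized is therefore easier to win than the pairwise comparisons that are planned.

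This is the only justification of the sample size, and it concerns the primary outcome. If β is really about 30% or more for the sized comparison, the Discussion claims a strength that the calculation does not supply, and readers of the results would have the wrong figure for the chance of missing an effect of pilot size.

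**Working it through.** **Inputs (section 2.2).** Difference d = 923.60 − 846.82 = 76.78 s. Sum of variances V = 65.77² + 99.23² = 4325.69 + 9846.59 = 14172.29. Root-mean-square SD = √(V/2) = 84.18 s. Standardised difference = 76.78/84.18 = 0.912.

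**Sample size formula.** n per group = (z_α + z_β)² × V / d², with z_β = 0.842 and d² = 5895.17.

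**Reproducing the stated figure**
- One-sided 5%: (1.645 + 0.842)² × 14172.29/5895.17 = 14.86, so **15**. This is the protocol's number.
- Two-sided 5%: (1.960 + 0.842)² × 14172.29/5895.17 = 18.87, so **19** (20 by noncentral t).
- Other two-sided choices of SD also miss 15: larger SD alone 27, smaller SD alone 12, simple average of the two 19.

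**Power at 15 per group, two groups, one visit, absolute values.** The standard error is √(14172.29/15) = 30.74 s, so d/SE = 2.498.
- One-sided: Φ(2.498 − 1.645) = Φ(0.853) = 80.3% (78.6% by t).
- Two-sided: Φ(2.498 − 1.960) = Φ(0.538) = 70.5%. By noncentral t it is 67.4% with 28 df (two groups only) and 69.0% with 56 df (error pooled over four groups).
- With all 72 recruits retained (18 per group), two-sided power is 75.8% (t) to 78.1% (normal), still below 80%.
- The difference detectable with 80% power at 15 per group, two-sided by t, is about 88–89 s, against the planned 76.78 s.

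**Adding Bonferroni.** The number of comparisons is an assumption, since section 2.6 does not give it. Two-sided power at 15 per group by t, with 28 and 56 df:

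| Comparisons assumed | Power |
|---|---|
| 1 (no correction) | 67–69% |
| 2 | 56–58% |
| 3 | 49–52% |
| 4 | 44–47% |
| 6 (all group pairs, one visit) | 38–41% |

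**Two alternatives that the protocol does not describe as its basis**
- Omnibus four-group F test at 5%, assuming A = C and B = D with the pilot means: 82.8% at 15 per group.
- Two-sided contrast A+C versus B+D (30 versus 30), same inputs: 93.5% (t) to 94.2% (normal).

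**The case against.** The strongest defence is that the primary test in section 2.6 is an ANOVA, not a pairwise t-test. Under A = C and B = D, an omnibus four-group F test has 79.6% power at 14 per group and 82.8% at 15, so 15 is the smallest size that reaches 80%. A reader might infer that 15 can come only from a one-sided calculation; that is too strong, and the statement holds only among two-mean calculations. The defence does not rescue section 2.2, however, which presents two pilot means and SDs and does not mention an F test over four groups.

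Second, a reader might infer that the trial has about 40% power. That figure requires all six group pairs to be corrected for, and the protocol does not say so. Two comparisons (A versus B, C versus D) would cover the detraining question, and three would cover comparisons with D. Multiplying six pairs by five visits to reach 30 comparisons is less supportable still, because one of the five visits is the pre-treatment baseline.

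Third, the figures above are for a single visit. The plan includes repeated measures and percentage change from baseline, whose power depends on a within-person correlation that is not reported. As an illustration with assumed correlations of 0.4, 0.5, 0.6, 0.7 and 0.8, uncorrected two-sided power for change from baseline at 15 per group would be 60%, 67%, 77%, 88% and 97%. So the documents do not establish that the planned analysis as a whole falls short of 80%.

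All three points limit the claim. None makes 15 per group the right answer to the two-mean calculation if that is two-sided.

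**Conclusion.** The concern holds for the comparison that was sized. On the stated inputs, 15 per group corresponds to a one-sided, uncorrected comparison of two means, which the analysis section does not plan. For a two-sided 5% comparison of two groups at one visit, 19 to 20 per group are needed, and 15 give about 67–70% power. Bonferroni takes this lower: from 56–58% for two comparisons to 38–41% for six.

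This rests on four assumptions:
- The tests are two-sided. This is inferred from the non-directional ANOVA and the absence of any one-sided declaration.
- The pilot means and SDs, from 5 volunteers per group, are taken at face value.
- Absolute values are compared at a single visit.
- For the Bonferroni figures, the number of comparisons is as assumed.

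A reader might go on to conclude that the trial is too small for its aim. The documents do not support that: the aim concerns detraining, and the pooled detraining contrast would have about 93% power with the planned 60.

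**What to change.** **In section 2.2**, state whether the calculation was one- or two-sided and which comparison it sized. Replace the implied 80% with about 67–70% for a two-sided single pairwise comparison at one visit, and say that it is lower after Bonferroni, naming the number of comparisons. Correct the Discussion sentence on power to match.

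**Alternatively**, pre-specify one two-sided primary contrast at week 16, the detraining effect A+C versus B+D (30 versus 30), and state its power of about 93%. Say that this assumes a similar detraining effect after either training regimen.

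**Cost.** Wording only, with no added enrolment. The first route makes the stated power less favourable; the second limits the primary claim to the pooled detraining contrast.

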### Randomization and blinding and experimental groups

2.4

To avoid selection bias and to ensure that all individuals are randomly allocated to any group, balanced block randomization will be performed based on the primary outcome (time to exhaustion in the progressive treadmill test) by a researcher who will have no contact with the study subjects or the other researchers involved in the project.

A researcher will program the device (PMBT or placebo) and will be instructed not to inform the volunteers or other researchers as to the type of treatment (PMBT or placebo). Therefore, the researcher responsible for the treatment will be blinded to the type of treatment being administered to the volunteers. The sounds and signals emitted from the device as well as the information displayed on the screen will be identical, regardless of the type of treatment (PMBT or placebo).

Randomization labels will be created through the random.org website, and a series of sealed, opaque, and numbered envelopes will be used to ensure confidentiality and will determine to which experimental group each volunteer will be allocated. Volunteers will be allocated as described below:

**A**: PBMT before and after the aerobic training sessions (12 weeks, 3 times a week) and PBMT during the detraining period (4 weeks, 3 times a week).**B:** PBMT before and after the aerobic training sessions (12 weeks, 3 times a week) and placebo during the detraining period (4 weeks, 3 times a week).**C:** Placebo before and after the aerobic training sessions (12 weeks, 3 times a week) and PBMT during the detraining period (4 weeks, 3 times a week).**D:** Placebo before and after the aerobic training sessions (12 weeks, 3 times a week) and placebo during the detraining period (4 weeks, 3 times a week).

The individuals randomly allocated to the different groups will be subjected to 12 consecutive weeks of aerobic endurance training in a motorized treadmill, with 3 training sessions per week on nonconsecutive days.

After the 12-week training period, the volunteers will receive the treatment, either PBMT or placebo, depending on the group to which they were allocated, during 4 weeks (3 times a week) without training.

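### Recruiting 72 men does not leave 60 after the predicted 20% loss: it leaves about 57.6, and 72 allows for a loss of only 16.7%

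*Protocol article*

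**What the plan says.** The section on subjects and sample size in the protocol article builds the recruitment figure in two steps.

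- **Base size.** From the pilot study, time to exhaustion was "923.60 seconds (65.77 standard deviation") with active treatment during detraining and "846.82 seconds (99.23 standard deviation") with placebo. On error rates the text says: "A β value of 20% and an α of 5% were used to calculate the sample size". The result: "we found 15 volunteers per group, for a total of 60 volunteers".
- **Allowance for loss.** The text continues: "predicting a 20% sample loss, 72 healthy, physically inactive male volunteers aged from 18 to 35 years will be recruited". The purpose is given as "to ensure a final sample size of 60 volunteers".

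The randomisation section describes four groups, A to D, and says that "balanced block randomization will be performed based on the primary outcome". With equal groups, 72 recruits are 18 per group. No other section gives a different loss rate or recruitment number.

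**The concern.** A loss rate normally applies to the people who enter. The sentence itself runs in that order: 72 enter, 20% are lost, 60 remain. Taken that way, the third figure does not follow from the first two. The recruited number looks like the required number raised by 20%, which is not the inverse of losing 20%.

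What is at stake is the number of men with usable data on the primary outcome. The article says that 60 will be ensured, and its discussion lists the sample-size calculation among the strengths of the study. At the plan's own attrition rate that number is not reached on average. Loss is also a realistic prospect here. Follow-up runs for 16 weeks, the eligibility section excludes men who are injured during the study and requires completion of at least 80% of procedures, and the treadmill-test section excludes men with abnormal readings or complaints.

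**Working it through.** **Inputs, all from the sample-size section.** Required final number 60 (15 × 4); predicted loss 20%; recruited number 72; pilot means 923.60 s and 846.82 s; pilot SDs 65.77 s and 99.23 s; α 5% (sidedness not stated); β 20%.

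**1. Reproducing the base size.**
- Difference: 923.60 − 846.82 = 76.78 s.
- Pooled SD: √((65.77² + 99.23²)/2) = 84.18 s.
- Standardised difference: 76.78/84.18 = 0.912.
- Formula per group: n = 2 × ((z for α + z for power)/0.912)².
- One-sided α 5%: 2 × ((1.645 + 0.842)/0.912)² = 14.86, rounded up to **15**. This is the article's figure.
- Two-sided α 5%: 2 × ((1.960 + 0.842)/0.912)² = 18.87, rounded up to 19. This is not the article's figure.

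**2. Reproducing 72.**
- Final number × (1 + loss): 60 × 1.20 = **72**, an exact match.
- Final number ÷ (1 − loss): 60/0.80 = 75, no match.

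**3. What 72 delivers.**
- Retained at 20% loss: 72 × 0.80 = **57.6**, or 57.6/4 = 14.4 per group.
- Shortfall: 60 − 57.6 = 2.4 men, or 0.6 per group.
- Loss that 72 can absorb: (72 − 60)/72 = **16.7%**.

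**4. What a 20% loss requires.**
- In total: 60/0.80 = **75**.
- Per group: 15/0.80 = 18.75, rounded up to 19, so **76** for four equal groups. Retained: 76 × 0.80 = 60.8.

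**5. Effect on power at the pilot difference.**

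| Calculation | 15 per group | 14.4 per group | Change (points) |
|---|---|---|---|
| One-sided 5%, normal approximation (reproduces 15) | 80.3% | 78.9% | 1.4 |
| One-sided 5%, Welch t | 78.3% | 76.7% | 1.6 |
| Two-sided 5%, Welch t | 66.9% | 65.0% | 1.9 |

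**6. Chance of keeping at least 60.** The article does not say how losses arise. Assuming that each man is lost independently with probability 0.20, the binomial probability of retaining 60 or more is about 0.30 with 72 recruited, 0.57 with 75 and 0.65 with 76.

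**The case against.** **The 20% may be a margin on the final 60.** Twelve is 20% of 60, and some authors use the percentage loosely in that way. No formula is printed, so multiplication by 1.2 is an inference from an exact match. This much stands: the cause cannot be stated as fact. The inconsistency does not depend on it. The text calls the 20% a predicted loss, and under either reading the share of recruits that can be lost is 16.7%.

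**The correct figure does not guarantee 60 either.** This stands. With 75 recruited, 60 is the average outcome, reached or exceeded in about 57% of trials under independent losses. The figures 75 and 76 are what the stated rate requires on average, and no number of this order ensures 60.

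**Analysis is by intention to treat.** The statistical section says so, which means that the analysis set is not plainly the completers. But the sample-size section sets its own target as the number remaining after loss, and a man without a final treadmill test still contributes less information.

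**The shortfall is trivial beside the uncertainty in a pilot with 5 men per group.** This largely stands, and it limits the weight of the point. It does not make the sentence correct.

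**A stronger reading to resist.** A reader might infer that this slip leaves the trial seriously underpowered, since two-sided power at 14.4 per group is only 65.0%. The figures do not support that. Two-sided power is already 66.9% at the full 15 per group. The gap from there to 80% comes from the base calculation, which matches the article only with a one-sided α. Any further reduction from correcting for multiple comparisons would likewise be present at 15 per group. Those are separate questions.

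**Conclusion.** The point holds as an internal inconsistency in one sentence: a 20% loss, 72 recruited and 60 remaining are incompatible. It rests on arithmetic alone, with the loss rate taken as a share of those recruited.

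The consequence is small, at 2.4 men and about 1.4 to 2 points of power. Those power figures assume the pilot difference and SDs and a simple two-group comparison. The correction is still worth making, because the sentence supports the sample size for the primary outcome and promises a number that the plan's own attrition rate does not deliver on average. It does not show that the design is invalid or that recruitment must rise.

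**What to change.** Restate the sentence in one of these ways:

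1. Keep 72 and say that it allows for a loss of 16.7% of those recruited.
2. Keep 72 and the 20% prediction, say that about 57 men (about 14 per group) are then expected to remain, and give the power at that number, with the sidedness of α.
3. If 60 completers at a 20% loss is really intended, change the recruitment figure to 75, or 76 for four equal groups.

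In each case, replace the claim that 60 is ensured with an expected number. The first two options cost one sentence and no extra volunteers. The third costs three or four more volunteers (75 − 72 = 3; 76 − 72 = 4).
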